## **5. SCREENING AND WITHDRAWAL OF PARTICIPANTS**

The participants must fulfil all eligibility criteria to be involved in this study. No exemptions from any in-/exclusion criteria will be allowed. If any protocol violations in enrollment are retrospectively detected for an already randomized participant, the investigator and Sponsor must determine immediately the safety of the participant in the subsequent study.

### **5.1 Participant Population**

#### **5.1.1 Inclusion Criteria**

Individuals are eligible to participate in this study if all of the following criteria apply:

- Age:  $\geq 18$  years;
- Judged by the investigator that the health condition is well after inquiry and physical examination;
- Vaccinated with 2 or 3 doses of inactivated COVID-19 vaccine (Vero Cell vaccine)  $\geq 6$  months prior to study screening and according to product insert;
- Female participants who are not pregnant or nursing or at the time of enrolment (confirmed via negative urine pregnancy test), and do not have plans to become pregnant within the first 6 months after enrollment. Effective contraceptive measures have been taken within 2 weeks before study inclusion and initiation;
- Be able and willing to provide written informed consent to participate in the study and complete all study requirements according to the study protocol.

#### **5.1.2 Exclusion Criteria**

Individuals are not eligible to participate in this study and are therefore excluded from study participation if one or more of the following criteria apply:

- COVID-19 infection positive patients (including suspected or asymptomatic cases);
- Have a history of SARS and MERS infection;

**CONFIDENTIAL**

- Have been vaccinated by any COVID-19 Vaccines other than Vero Cell vaccine
  - Have an axillary temperature  $\geq 37.3^{\circ}\text{C}$  (forehead temperature  $\geq 37.8^{\circ}\text{C}$ );
  - Have had previous allergic reactions to vaccination (such as acute allergic reactions, urticaria, eczema, dyspnea, angioneurotic oedema or abdominal pain) or allergy to known components of COVID-19 vaccine;
  - History of thrombocytopenia or other coagulation disorders;
  - Patients with known immunological impairment or immunocompromised.
  - Received whole blood, blood products, plasma and/or immunoglobulin therapy within 3 month before study enrollment
  - Have known or suspected severe illness such as respiratory illness, acute infection or active attacks of chronic illness, liver and kidney disease, severe diabetes mellitus, malignant tumour, infectious or allergic skin disease, human immunodeficiency virus (HIV) infection (test report available);
  - Diagnosed with serious cardiovascular diseases such as cardiopulmonary failure, drug-uncontrolled hypertension (Systolic blood pressure  $\geq 160$  mmHg and/or diastolic blood pressure  $\geq 95$  mmHg).
  - Received live attenuated vaccines within 1 month before study enrollment;
  - Received inactivated vaccines within 14 days before study enrollment;
  - Received other investigational drugs within 6 months before study enrollment;
- Other vaccination-related contraindications considered by investigators.

### 5.1.3 Criteria for Early Withdrawal from the Trial

Early withdrawal means that the participant fails to complete the booster vaccination and blood collection procedures according to the clinical study protocol and permanently discontinues study participation.

When any of the following conditions occur, the participant will be withdrawn from the study.

- The participant requests to withdraw from the clinical trial;
- Intolerable adverse events, whether related to the investigational drug or not;
- The health status of the participant does not allow them to continue to participate in this trial;
- The participant is vaccinated with other clinical investigational vaccines during the study

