| Product Characteristic | The universal recombinant protein used to develop the COVID-19 NVSI-06-09 vaccine was expressed by recombinant Chinese hamster ovary (CHO) cells and designed based on the receptor-binding domain (RBD) of SARS-CoV-2 Spike (S) protein. Engineered cells were cultured, harvested and purified by a series of processes, and then added with aluminum hydroxide adjuvant. The product is a universal recombinant COVID-19 vaccine against major variants such as the SARS-CoV-2 Omicron variant. It is developed through in-depth research on virus structure, mutation pattern and mutation sites, especially based on the analysis of mutations at the receptor-binding domain of the SARS-CoV-2 Omicron variant. |
| Indications            | The universal recombinant COVID-19 (NVSI-06-09) vaccine can be used to immunize adults aged 18 years and above. Immunization with this vaccine can stimulate the body to produce an immune response to SARS-CoV-2 for the prevention of COVID-19 infection.                                                                                                                                                                                                                                                                                                                                                                                                                                                           |
| Study Design           | 
This is a randomized, double-blind parallel, and positive controlled study design. Participants who have been previously vaccinated with two or three doses of Vero cell vaccine (<math>\geq 6</math> months prior to the study screening visit) will receive one booster dose of either NVSI-06-09 vaccine or Vero Cell vaccine.
 
Sample Size: A total of 516 participants will be randomly assigned to one of two study groups (NVSI-06-09 vaccine group or Vero Cell vaccine group) in a 1:1 ratio, with 258 participants in each group.
 
Immunization Schedule: Participants will be immunized with one booster dose of either NVSI-06-09 vaccine or Vero Cell vaccine.
          |

CONFIDENTIAL

**Route of Administration:** Vaccines will be administered via intramuscular injection in the lateral deltoid muscle of the upper arm.

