| 
early withdrawal
                              | 
study.
 
 
- The participant requests to withdraw from the clinical trial;
 
- Intolerable adverse events, whether related to the investigational drug or not;
 
- The health status of the participant does not allow them to continue to participate in this trial;
 
- The participant is vaccinated with other clinical investigational vaccines during the study period;
 
- Any other reason that investigator considers.
 
                                                                                                                                                                                                                                                                                                                                                                                                                                                                                                                                                                                               |
| 
Criteria for suspension and early termination
 | 
In case of any of the following circumstances, the trial shall be suspended, the investigator, the Sponsor and the Ethics Committee shall jointly hold a meeting to decide whether to terminate the clinical trial early:
 
 
- The number of participants with adverse reactions of severity rated Grade 3 or above exceeds 15% of the participants study vaccinated in this subgroup;
 
- One case of Grade 4 adverse reaction related to vaccination or a suspected unexpected serious adverse reaction (SUSAR) has occurred.
 
 
In case of any of the following circumstances, the clinical trial shall be terminated early:
 
 
- The Sponsor has found that the vaccine has potential safety hazards or the trial has quality-related problems and requires the complete termination of the study.
 
- The Ethics Committee requests to terminate the trial because of the ethical violation in the trial.
 
- The administrative authority requests to terminate the trial.
 
 |

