### 4.3. Study Endpoint

**CONFIDENTIAL**

**Primary Endpoints:**

1. GMT and the 4-fold rise rate of anti-omicron neutralizing antibody 14 days after a single dose of the booster vaccine in adults  $\geq 18$  years of age.
2. The incidence and severity of any adverse reactions/events within 30 minutes after vaccination;
3. The incidence and severity of solicited adverse reactions/events within 0-7 days after vaccination;
4. The incidence and severity of unsolicited adverse reactions/events within 8-30 days after vaccination;
5. The incidence of SAE and AESI observed after vaccination and up to 12 months after full course of immunization.

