**CONFIDENTIAL**

respectively, the participants were followed-up by telephone and guided to observe the adverse events correctly and fill in the diary card.

3. On the 14th day after vaccination, the investigator reviews the filling of the diary card during this period and re-collect the diary card.
4. On the 8th -28th day after vaccination, the investigator uses telephone follow-up once a week, combined with an active report of the participants to monitor the safety.
5. When it is known that the participant has adverse reactions/events of Grade 3 or above, a face-to-face visit should take place within 24 hours.
6. SAEs and AESIs are observed from the first dose to 12 months after the full course of vaccination via monthly telephone follow-up calls and self-reports from the participants.
7. Participants should contact the doctors on informed consent form/diary card immediately if developed any COVID-19 like symptoms.

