## **(2) Reporting Procedures for Serious Adverse Events**

### ***Reporting procedures of investigators include:***

Any serious adverse event, whether related to the investigational vaccine, the investigator must submit the initial report of the "Serious Adverse Event Report Form" to the drug administration department, the Sponsor and the ethics committee by fax, e-mail or EDC system or personal delivery within 24 hours after learning about it. Subsequently, the follow-up report of the "Serious Adverse Event Report Form" shall be submitted regularly until the end of the event. All information is reported in the "Serious Adverse Event Report Form" in the form of written reports, including description of adverse reactions/events, onset time and type, duration, intensity, causal relationship with vaccination, results, treatment methods (symptomatic treatment) and other relevant clinical and laboratory data. When receiving the report of serious adverse events/reactions, the investigator shall, together with the Sponsor, comprehensively consider the duration, scope, intensity, outcome and the willingness of the participant to decide whether the participant should continue to participate in the study or withdraw from the study in advance.

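### The early-withdrawal rule takes participants out of the study for adverse events or poor health after the only dose, and no provision keeps them in the 12-month SAE/AESI follow-up

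*Protocol*

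**What the plan says.** Protocol section 5.1.3 states: "When any of the following conditions occur, the participant will be withdrawn from the study". The list includes "Intolerable adverse events, whether related to the investigational drug or not" and, as a separate ground that concerns general fitness, "The health status of the participant does not allow them to continue to participate in this trial". Further grounds are receipt of another investigational vaccine and any other reason the investigator sees. The synopsis repeats the list. Both describe an early withdrawal as someone who fails to complete vaccination and blood collection and "permanently discontinues study participation".

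The intervention is a single injection at Visit 1: "Participants will be immunized with one booster dose of either NVSI-06-09 vaccine or Vero Cell vaccine".

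The safety objective runs much longer. Primary endpoint 5 (section 4.3) is "The incidence of SAE and AESI observed after vaccination and up to 12 months after full course of immunization". Section 7.3.1, item 6, collects these events to 12 "months after the full course of vaccination via monthly telephone follow-up calls and self-reports from the participants". Section 7.10 makes site closure depend on all participants having completed 12 months of safety observation.

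Section 8.3 (1) has SAEs followed until symptoms disappear or stabilise. Section 8.3 (2) has the investigator and sponsor together "decide whether the participant should continue to participate in the study or withdraw from the study in advance" after an SAE.

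Section 10.2 puts every vaccinated participant in the Safety Set. Section 10.7 leaves missing safety data unimputed and applies LOCF to missing post-vaccination antibody values in the FAS.

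**The concern.** In a multi-dose trial, withdrawal for intolerable adverse events also stops further exposure. Here no dose remains after Visit 1, so the rule can only end calls, visits and blood draws. It does so for participants selected on adverse events or failing health, while a primary endpoint asks what happens to all vaccinated participants over 12 months.

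Loss of follow-up then depends on how the participant fared, and an analysis plan cannot recover events that were never collected. If the two vaccines differ in reactogenicity, the loss could also differ by arm. The protocol gives no information on whether they do.

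**Working it through.** **1. The passages side by side**

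| Place | What it requires |
|---|---|
| 5.1.3 and synopsis | Withdrawal is mandatory once a listed condition occurs; participation ends permanently |
| 8.3 (2) | After an SAE, continuing or withdrawing is a joint, case-by-case decision |
| 4.3, endpoint 5 | SAEs and AESIs counted to 12 months |
| 7.3.1, item 6 | SAEs and AESIs sought by monthly calls and self-report to 12 months |
| 7.10 | All participants complete 12-month safety observation |
| 8.3 (1); 7.3.2 | A known SAE is followed until it disappears or stabilises; persistent reactions within days 0-28 are followed until relieved |

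The first row does not fit the next four. The last row covers events already known. No section separates leaving study procedures from leaving safety follow-up, and none provides for finding a new SAE or AESI after withdrawal.

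**2. What one withdrawal removes**

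For withdrawal on day 7, taking 12 months as day 360 (the numbering rule in 7.4): 360 − 7 = 353 days, and 353/360 = 98% of the SAE/AESI window. All six post-booster bloods are lost (day 14, day 28, months 3, 6, 9 and 12).

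**3. Share of later events missed**

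The plan states no figure for this. Its 258 per arm is used only to convert shares to counts, and it reproduces from section 10.1: 2 × (1.960 + 1.282)² × 0.55² / 0.17609² = 205.01, so 206 per group; 206/0.8 = 257.5, so 258, or 516 in total.

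Assumptions: a fraction w is withdrawn early; their later risk is r times that of those who stay; none of their later events is seen; the 12-month SAE/AESI risk in those who stay is p₀ = 2%.

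True later events per arm = 258 × [(1 − w)p₀ + w·r·p₀]; seen = 258 × (1 − w)p₀.

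Share missed = w·r / (1 − w + w·r). It does not depend on p₀.

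| w (number per arm) | r = 1 | r = 5 | r = 10 |
|---|---|---|---|
| 1% (2.6) | 1.0% | 0.05/1.04 = 4.8% | 0.10/1.09 = 9.2% |
| 2% (5.2) | 2.0% | 0.10/1.08 = 9.3% | 0.20/1.18 = 16.9% |
| 5% (12.9) | 5.0% | 0.25/1.20 = 20.8% | 0.50/1.45 = 34.5% |

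In counts, with p₀ = 2%, missed events are 258·w·r·p₀: 0.05 per arm (w = 1%, r = 1), 1.3 of 6.2 (w = 5%, r = 5) and 2.6 of 7.5 (w = 5%, r = 10).

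**4. Titres**

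FAS membership needs vaccination and a valid pre-dose titre (10.2). For someone withdrawn before day 14, baseline is the only value LOCF can carry forward, so that person enters as having no rise. The PPS drops them.

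Illustration without covariate adjustment: if such withdrawals differ by 2 percentage points between arms and those who stay rise 4- to 10-fold, the log10 difference shifts by 0.02 × 0.602 = 0.012 to 0.02 × 1 = 0.020. That is close to the superiority margin of 0.0212, but below half of one standard error at 258 per arm (0.55 × √(2/258) = 0.048).

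**The case against.** Several counter-arguments carry weight.

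- The event that triggers withdrawal is recorded. Section 10.3.4 reports participants with events, so someone withdrawn because of an SAE or AESI is already in the numerator. A reader might infer that the worst-affected participants vanish from the count and appear event-free. The protocol does not support that. Only a later event, or a first SAE or AESI after a non-serious trigger, can be missed.
- A reader might also infer that a whole AESI signal could be hidden, or that the comparison is biased by arm. The protocol gives no withdrawal rate, no SAE/AESI rate and no difference in reactogenicity, so neither can be asserted.
- Primary endpoints 2 to 4 close by day 30 and are touched only by withdrawal before then.
- After an SAE, section 8.3 (2) allows case-by-case judgement that weighs the participant's willingness, and 7.10 presupposes that all participants are observed for 12 months. The intent may be to keep observing. This shows that the passages disagree; it does not settle what a site does under 5.1.3.
- Stopping blood draws in an unwell participant has a purpose of its own. That stands, and it is why procedures and safety contact should be treated separately.
- The 20% drop-out allowance (258 − 206 = 52 per arm) exceeds any withdrawal number assumed here. It protects power; it does not correct loss related to outcome.

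**Conclusion.** The point holds in limited form. Read literally, 5.1.3 and the synopsis end 12-month SAE/AESI observation for participants selected on adverse events or health, after a dose that cannot be undone. This contradicts endpoint 5, 7.3.1 and 7.10, and does not fit the joint decision in 8.3 (2). Later unseen events count as none in the Safety Set, and an FAS participant withdrawn before day 14 has only a baseline titre to carry forward.

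The size is unknown. On assumed early withdrawal of 1% to 5%, about 1% to 5% of later events are missed at equal risk and 5% to 21% at five-fold risk. The loss exceeds the withdrawn share whenever those withdrawn are at higher risk, which selection on health makes plausible but the protocol does not quantify. The planned sample size is not in question here.

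**What to change.** Reconcile 5.1.3, the synopsis, 7.10 and 8.3 (2) with primary endpoint 5 by distinguishing withdrawal from study procedures from withdrawal from safety follow-up:

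- Unless the participant withdraws consent to contact, SAE/AESI follow-up continues to 12 months through the calls that 7.3.1 already provides for.
- The day-14 and day-28 bloods are taken where the participant is willing and the investigator judges it appropriate.
- The reason for withdrawal is recorded, and titres taken after another investigational vaccine are flagged.

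The clinical criteria themselves, and the investigator's discretion over procedures, remain for the sponsor to settle.

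The cost is protocol wording. The calls and bloods are already planned for everyone. The downside is continued contact with a few participants who would otherwise have been closed out.

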**CONFIDENTIAL**

period;

- Any other reason that investigator considers.

#### **5.1.4 Criteria for Clinical Trial Suspension and Termination**

In case of any of the following circumstances, the clinical trial shall be suspended or terminated, and the investigator, the Sponsor and the Ethics Committee shall jointly hold a meeting to decide whether to terminate the clinical trial early:

- The number of participants with adverse reactions of severity rated Grade 3 or above exceeds 15% of the participants study vaccinated in this subgroup;
- One case of Grade 4 adverse reaction related to vaccination or a suspected unexpected serious adverse reaction (SUSAR) has occurred.

In case of any of the following circumstances, the clinical trial shall be terminated:

- The Sponsor found that the vaccine has a potential safety hazard, or the trial has quality-related problems and requires the complete termination of the study.
- The Ethics Committee requests to termination of the trial because of the ethical violation in the study.
- The administrative authority requests termination of the trial.

## **6. PRODUCT INTRODUCTION**

### **6.1 Description and Characteristics of the Investigational Products**

Recombinant COVID-19 Vaccine (NVS1-06-09) is a recombinant protein expressed by recombinant Chinese hamster ovary (CHO) cells and designed based on the receptor-binding domain (RBD) of S protein of SARS-CoV-2. Engineered cells were cultured, harvested and purified by a series of processes, and then added with aluminum hydroxide adjuvant.

This product is a universal recombinant COVID-19 vaccine against major variants such as Omicron. It is developed through in-depth research on virus structure, mutation patterns and mutation sites, especially based on the analysis of mutations at Omicron's receptor-binding domain. On the premise of ensuring safety, it is more universal, effective and durable than the existing

**CONFIDENTIAL**

recombinant vaccines, especially has significant protection potential against variants including Omicron and Delta, it is believed that this vaccine will play a key role in epidemic prevention and control.

This product is a sterile formulation, packed in a vial with a specification of 0.5 ml/dose/vial. After shaking, it is an opalescent suspension, which can be layered due to precipitation and easily shaken away without lumps.

The main active ingredient of this product is the recombinant protein formed by the receptor-binding region of SARS-CoV-2 spike protein. Excipients include sodium chloride, aluminum hydroxide adjuvant, histidine, etc. Each dose contains 20µg of recombinant protein, 4.38 mg of sodium chloride, 0.39 mg of histidine, 0.30 mg of aluminum and water for injection. Used to prevent diseases caused by SARS-CoV-2.

#### **6.1.1 Investigational Vaccine**

**Investigational Vaccine:** Recombinant COVID-19 Vaccine (NVSI-06-09)

Manufacturers: Sinopharm CNBG National Vaccine and Serum Institute (NVSI),

Lanzhou Institute of Biological Products Co., Ltd. (LIBP),

Beijing Institute of Biological Products Co., Ltd. (BIBP),

Specifications: 0.5 ml/vial per human use, which contains 20ug of SARS-CoV-2 antigen.

Storage Condition: 2-8 °C.

Batch Number:

Expiry Date:

**Control vaccine:** Inactivated COVID-19 Vaccine (Vero cell)

Manufacturer: Beijing Institute of Biological Products Co., Ltd.

Specifications: 0.5 ml/vial per human use, which contains 6.5U of inactivated SARS-CoV-2 antigen.

Storage conditions: 2-8 °C

Batch Number:

**CONFIDENTIAL**

Expiry Date:

### 6.1.2 Production Process

The Recombinant COVID-19 Vaccine (NVSI-06-09) developed in this project takes CHO cells as the express system and SARS-CoV-2 spike protein as the target, applying genetic engineering technology to construct and screen stable cell lines with recombinant expression protein. After culture, harvesting and a series of purification processes and adding aluminum hydroxide adjuvant, the vaccine is finished after filling.

## 6.2 Vaccine Packaging and Labeling

All investigational vaccines are packaged in doses in boxes with the same appearance and only marked by the vaccine number. Each study ID will be matched with a unique vaccine number, the format of the vaccine number is AE+4-digit Arabic number. See the following label for detailed information.

